### **9.7. Timing of primary analysis**

The primary analysis for the study will occur once all participants have completed the 16 week assessment and the corresponding outcome data has been entered onto the study database and validated as being ready for analysis. This is provided the study has not stopped recruitment early for any reason (e.g. DMC advice or funding body request); if this is the case the analysis will be completed once the existing randomised participants have completed the 16 weeks assessment.

### **9.8. Timing of other analyses**

N/A

### **9.9. Covariate adjustment**

In the first instance, comparative estimates of differences between groups will be adjusted for the baseline values of the outcome variable of interest where available. If there are any imbalances at baseline in other important variables e.g. acetazolamide use, then these will also be included in the regression model as covariates.

### **9.10. Handling missing data**

In the first instance, analysis will be completed on received data only with every effort made to follow-up participants even after protocol violation to minimise any potential bias. Participants will naturally be excluded from the primary analyses if they have no data available at the relevant assessment times or they withdraw/are withdrawn from the trial prior to the primary assessment

time. To examine the possible impact of missing data on the results, and to make sure we are complying with the intention-to-treat principle, sensitivity analysis will be performed on the primary outcome measure. See section 10.8 for further details.

### 9.11. Distributional assumptions and outlying responses

Distributional assumptions (e.g. normality of regression residuals for continuous outcomes) will be assessed visually prior to analysis; although in the first instance the proposed primary method of estimation in this analysis plan will be followed. If responses are considered to be particularly skewed the impact of this will be examined through sensitivity analysis; this will consist of transformation of responses prior to analysis (e.g. log transformation) in the first instance. If extreme values are apparent and considered to be affecting the integrity of the analysis, sensitivity analysis consisting of removing the outlying response(s) and repeating the base analysis will be performed. Output from these analyses, if performed, will be described and presented alongside the base case analysis (or included, e.g. in appendices) with the excluded values clearly labelled. See section 10.8 for further details.

### 9.12. Data manipulations

The Trial Statistician will derive all responses from the raw data recorded in the database. The specifics of the data manipulations required are as follows.

Scoring for the following questionnaire responses will be calculated as per the following (refer to references for details):

- HIT-6: a six-item questionnaire with the following choice of responses: Never=6; Rarely=8; Sometimes=10; Very Often=11; and Always=13. Response scores from each of the questions are summed to produce the disability score. Score of 36=best outcome, and a score of 78=worst outcome;
- Headache Diary: diary is completed over 7 days prior to visit with information on severity and duration of headache, and use of painkillers. The total severity score is the severity summed up over the week divided by the number of days where headache was recorded, and the total duration score is the duration summed up over the week divided by the number of days where headache was recorded. If either severity or duration is missing, it is considered to be zero severity or duration for that day. The headache frequency is just the summation of the number of days a headache is experienced that week. In line with international Headache society reporting guidelines on headache outcomes which recommends reporting headache frequency per month, the weekly headache frequency will then be multiplied by 4 to provide a headache frequency per month (which will then be comparable with other trial datasets). Similarly, analgesic use will be calculated by summing up the number of times they are used over a week, then multiplied by 4 to provide analgesic use per month.

There are 2 versions of the headache diary. The first scored severity on a 0-5 scale. The second on a 0-10 scale. To combine the scores, the first version 0-5 scores will be mapped onto the second version scores using the following method: 0=0; 1=2; 2=4; 3=6; 4=8; and 5=10.

- Frisen Grading is scored on a 0-5 integer scale with 0=normal optic disk and 5=severe papilloedema.

Other outcomes will be calculated as follows:

- Age – number of days from date of birth to randomisation date divided by 365.25 to give age in years;
- Duration of IIH – number of days from date of diagnosis of IIH to randomisation date divided by 30.4 to give duration of IIH in months;
- Worst eye – the eye that has the worst Mean Deviation score on the Humphrey Visual field assessment at baseline will be considered the 'worst eye' for all analyses;
- Best (fellow) eye – the eye that has the better Mean Deviation score on the Humphrey Visual field assessment at baseline will be considered the 'best eye' for all analyses.

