## 6.2. Secondary outcomes

Secondary outcomes are as follows:

- IIH symptoms (presence or absence of tinnitus, perceived visual loss, diplopia, visual obscuration and headache) over 12 weeks, and at 16 weeks;
- IIH visual function in both eyes (measured by LogMAR (log of the minimum angle of resolution) chart to assess visual acuity, automated perimetry (Humphrey 24-2 central threshold) to measure the visual field mean deviation and MARs charts to evaluate contrast sensitivity) between baseline, week 12 and week 16;
- Papilloedema evaluated using 1). spectral domain optical coherence tomography and 2). Fundus photographs with Frisen classification (by masked neuro-ophthalmologists to grade the images and who also assess whether the image is better, worse or the same as the image taken at baseline) between baseline, week 12 and week 16;
- Headache associated disability using the headache impact test-6 score (HIT 6), headache diary (to assess headache frequency (days/week), severity and duration) and use of analgesia (days/week) between baseline and 12 weeks, with further analysis between weeks 12 and 16;
- Anthropological measures (e.g. blood pressure, body mass index (BMI), waist/hip ratio and fat distribution);
- Safety and tolerability of AZD4017 measured using adverse event (AE) and serious adverse event (SAE) reporting and safety bloods.

Fundus photographs will be reviewed by three masked neuro-ophthalmologists who will grade the images as described above. The overall grading of an image will be where the majority of the neuro-ophthalmologists are in agreement on a grade, or in the instance where the neuro-ophthalmologists are in disagreement by at most one grade, the median will be taken as the grade. If the neuro-ophthalmologists disagree by more than one grade, these images will be checked by a 4th neuro-ophthalmologist to obtain a consensus grade.

The HIT 6 is a patient completed questionnaire where a score of 36=best outcome, and a score of 78=worst outcome.

The Headache Diary is completed over 7 days at baseline (participants complete daily headache diary in week before screening visit) and weeks 12 and 16 (participants complete daily headache diary in week prior to visit). Severity (0-5)\* and duration (over each 24 hour period) of headache are reported for each day, along with use of painkillers.

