### 10.8. Sensitivity analyses

Sensitivity analyses will be limited to the primary outcome and will consist of:

- Per-protocol analysis (population described in section 9.2);
- An analysis to assess the effect of missing responses using multiple imputation and last observation carried forward (the primary outcome is only collected at baseline and 12 weeks, so this is carrying forward the baseline ICP to 12 weeks, which is essentially assuming no change);
- An analysis to assess the effect of late assessments by including only those returned within the assessment window in the analysis.
- An analysis to assess the effect of any distributional assumptions (details provided in section 9.11);
- An analysis to assess the effect of any outliers.

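### The headache diary rule scores a skipped severity or duration item as zero yet keeps the day in the denominator, which pulls both weekly scores down

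*SAP*

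**What the plan says.** SAP section 6.2 makes headache frequency, severity and duration, and analgesic use, part of a secondary outcome. They come from a 7-day diary kept before the screening, week 12 and week 16 visits. The daily entries it lists are severity, duration and painkiller use.

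Section 9.12 gives the derivations:

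- Severity: "The total severity score is the severity summed up over the week divided by the number of days where headache was recorded".
- Duration: "the total duration score is the duration summed up over the week divided by the number of days where headache was recorded".
- Missing items: "If either severity or duration is missing, it is considered to be zero severity or duration for that day".
- Frequency: "The headache frequency is just the summation of the number of days a headache is experienced that week". This is then multiplied by 4 to give a monthly figure. Analgesic use is summed over the week and multiplied by 4 in the same way.
- Scale: "The first scored severity on a 0-5 scale. The second on a 0-10 scale". Version 1 scores are doubled, so zero stays zero and is the floor of both versions.

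Two general sections bear on the rule. Section 9.10 says: "In the first instance, analysis will be completed on received data only". Section 10.8 says: "Sensitivity analyses will be limited to the primary outcome and will consist of", and the list that follows concerns ICP only.

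The change log presents the version 2.0 addition as standard definitions for calculating headache severity and duration. The SAP gives no reason for the zero rule itself.

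**The concern.** The zero rule and the denominator do not fit together. Each score is meant to describe a typical headache day, so it is averaged over headache days. If a participant recorded a headache but left one of the two items empty, the day still counts as a headache day, and the missing item enters as 0. That value is the best possible one, and it is impossible on a day already accepted as a headache day.

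The result is single imputation with the most favourable value, built into the derivation, so every later analysis inherits it. Section 10.6 analyses continuous secondary outcomes as the primary outcome is analysed, by linear regression on the week 12 (or 16) value with baseline as covariate. With 15 participants per arm planned, a few incomplete diaries could move an arm mean, and no planned analysis would show that they had.

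**Working it through.** The SAP gives no figure for the size of this effect and no rate of missing diary items, so there is no stated number to reproduce. The check follows the section 9.12 formulas on assumed values: severity 6 (0–10 scale) and duration 8 hours on every headache day.

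**1. A headache day with one item skipped.** Let h be the number of headache days and m the number of those with the item missing. At a constant true value s:

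score under the SAP rule = s × (h − m) / h

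score over recorded items only = s × (h − m) / (h − m) = s

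| h | m | Severity under the rule | Duration under the rule (h) | Change |
|---|---|---|---|---|
| 7 | 1 | 36/7 = 5.14 | 48/7 = 6.86 | −14% |
| 7 | 2 | 30/7 = 4.29 | 40/7 = 5.71 | −29% |
| 7 | 3 | 24/7 = 3.43 | 32/7 = 4.57 | −43% |
| 5 | 1 | 24/5 = 4.80 | 32/5 = 6.40 | −20% |
| 5 | 2 | 18/5 = 3.60 | 24/5 = 4.80 | −40% |
| 5 | 3 | 12/5 = 2.40 | 16/5 = 3.20 | −60% |
| 3 | 1 | 12/3 = 4.00 | 16/3 = 5.33 | −33% |
| 3 | 2 | 6/3 = 2.00 | 8/3 = 2.67 | −67% |

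Averaging over recorded items returns 6 and 8 hours in every row. The fewer headache days a participant has, the more each skipped item costs.

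**2. Direction over time.** Take 7 headache days at each visit and no true change. Two severity items skipped at week 12 give 30/7 − 6 = −1.71, an apparent improvement. The same two skipped at baseline give 6 − 30/7 = +1.71, an apparent worsening.

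**3. Direction between arms.** With 7 headache days and severity 6 in both arms, one more skipped item per participant in one arm gives a spurious difference of 6/7 = 0.86 points. With one skipped item per participant in both arms, a true difference D shrinks to D × 6/7 = 0.86 D. Variation in m between participants adds noise in either case.

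**4. A wholly blank day.** No headache is recorded, so the day leaves the denominator as well as the sum. With one such day, severity is 36/6 = 6, so these scores are not diluted. Frequency is: a participant with headache every day has a true monthly figure of 4 × 7 = 28, but 1, 2 or 3 blank days give 4 × 6 = 24, 4 × 5 = 20 or 4 × 4 = 16. A blank day likewise adds nothing to the analgesic total.

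**5. A headache-free day.** It adds nothing to the sum and is not in the denominator. Scoring its empty items as zero changes nothing.

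On this reading of the denominator, the rule has an effect only in case 1, where it is wrong.

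**The case against.** The strongest defence is that the rule was meant for headache-free days, on which a participant may well leave severity and duration empty. Zero is then true and harmless. Section 9.12 does not say which case is meant, and section 6.2 lists no separate yes/no headache item, so the frequency of partly completed headache days is unknown. This limits the size of the concern but does not rescue the rule: for headache-free days the sentence is redundant, and its reference to either item being missing also covers partly completed days.

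A different definition of a headache day does not help either. Suppose a day counted only if severity was positive. A day with 8 hours recorded but severity empty would add its hours to the duration sum and drop out of the denominator: 56/6 = 9.33 hours instead of 8. The distortion changes direction.

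Four stronger readings may tempt a reader, and the SAP does not support them:

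- *Incomplete diaries always look like improvement.* This holds for items skipped at week 12 or 16. Gaps at baseline push the other way.
- *Any blank day lowers severity and duration.* Only a recorded headache day with the item skipped does so. Wholly blank days affect frequency and analgesic use instead.
- *The rule contradicts section 9.10.* That section deals mainly with participants who have no data at an assessment and is worded as a first step. An item-level scoring rule beside it is a tension, not a contradiction.
- *Diary completion will differ by arm, for example because side effects reveal the allocation.* The trial is double-blind with matching placebo, and nothing in the SAP suggests this. Differential missingness is a condition for a spurious difference, not something the document shows.

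**Conclusion.** The point holds in a limited form. As written, the rule can only lower the weekly severity and duration scores when a recorded headache day has an item skipped, by the factor (h−m)/h at constant severity. On the assumed values with 7 headache days, that is 14% to 43% for one to three skipped items. It creates a spurious difference between arms only if missingness differs by arm; otherwise it weakens a true difference and adds noise. Separately, wholly blank days are counted as free of headache and of analgesics in the frequency and analgesic totals.

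These sizes rest on assumed severity, duration and numbers of skipped items, so they show what the rule can do, not what it will do in this trial. The primary outcome (ICP at 12 weeks), the sample size and HIT-6 are untouched. It should be fixed, but it does not threaten the trial's main conclusion.

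**What to change.** Replace the missing-item sentence in section 9.12 with:

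> A missing severity or duration on a day with recorded headache stays missing; the weekly severity (or duration) score is the mean over headache days on which that item was recorded. A day counts as headache-free only when the participant recorded no headache; a wholly blank day is missing.

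The section should also say which diary entry makes a day a headache day. Any minimum number of completed days, and any proration of frequency and analgesic use for missing days, is for the sponsor to choose and justify before unblinding. The SAP contains nothing that settles either, and proration assumes that missing days resemble completed ones.

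The cost is a few sentences of SAP text and a few lines of derivation code. The downside is that a few participants may become missing on a diary score, which matters somewhat in a trial of 30. The number of skipped items and blank days by arm and visit should be reported so that readers can judge the effect.

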## **10. Proposed statistical methods**

### **10.1. Study population**

A flow diagram (recommended by CONSORT) will be produced to describe the patient flow through each stage of the study. A template for reporting is given in Appendix D.

Numbers and description of reasons (where available) will be produced at each stage, e.g. reasons for withdrawing from the trial or why patients did not receive the allocated treatment. The following items (numbers of patients) will be described:

- Assessed for eligibility
- Eligible
- Randomised (by arm)
- Received allocated treatment/did not receive allocated treatment (by arm)
- Withdrawn/lost to follow up (by arm)
- Included in the primary analysis (by arm)

### **10.2. Baseline characteristics**

The study population will be tabulated. Demographic variables will be described for the total population and for the two randomised arms separately. This will include age (years); ethnicity; BMI (kg/m^2); Weight (kg); presence of IIH symptoms; whether or not the participant was taking acetazolamide; opening ICP (cmCSF); HIT-6 score; and Frisen grading.

Categorical data will be summarised by number of responses, frequencies and percentages.

Continuous data will be summarised by the number of responses, mean and standard deviation if deemed to be normally distributed and number of responses, median and interquartile range if data appear skewed. Tests of statistical significance will not be undertaken.

### **10.3. Compliance to allocation**

A cross-tabulation of allocated treatment by the compliance categories stated in section 9.2 will be produced (proportions and percentages). The mean number of doses and the mean percentage of total dose will also be reported.

### **10.4. Protocol deviations and violations**

Frequencies and percentages by group will be tabulated for the protocol deviations.

### **10.5. Analysis methods – primary outcome**

The primary outcome is ICP at 12 weeks. ICP is measured by lumbar puncture in cmCSF. The number of observations, mean and standard deviation of the ICP at baseline and 12 weeks by treatment arm will be presented. A linear regression model will be used to compare the ICP at 12 weeks between the two arms, adjusting for baseline ICP. See 9.9 for more details on covariate inclusion.

### **10.6. Analysis methods – secondary outcomes**

Continuous data items (e.g. HIT 6) will be analysed in the same way as the primary outcome. Analyses will be performed on data at 12 and 16 weeks. For the visual function data which is collected in both eyes, it is expected that the participant's data will be correlated, so the primary analysis will use data from both eyes, and will be analysed using a linear mixed model, with participant included as a random effect. The visual function and papilloedema data for worst eye and best eye will also be analysed separately as per the primary outcome, but this will be a secondary analysis.

The IIH symptom data is binary. The number and percentage of those with each symptom present will be presented at baseline and 12 and 16 weeks by treatment arm. Log-binomial models will be used to compare the symptom data at 12 and 16 weeks between the two arms, with baseline symptom included in the model as a covariate.

The Fundus photographs are given a Frisen Grading (score of 0-5) and the photographs at 12 and 16 weeks are compared to the baseline photograph to assess whether the image is better, worse or the same as the one taken at baseline (see section 6.2). These data items will be presented as categorical data items at each time point. A mean Frisen Grading will also be reported, and the data analysed as per the primary outcome. The same, better or worse data will be analysed at 12 and 16 weeks using a chi-squared test.

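### Section 10.6 writes the both-eyes mixed model for visual function only; for papilloedema it names a plain regression (Frisen grade) or no specific model (OCT) and never fixes the eye unit

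*SAP*

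**What the plan says.** Section 6.2 of the SAP lists visual function and papilloedema as separate secondary outcomes. Visual function is introduced as "IIH visual function in both eyes (measured by LogMAR (log of the minimum angle of resolution) chart to assess visual acuity", followed by perimetry and contrast sensitivity. Papilloedema has its own bullet, covering OCT and Frisen-graded fundus photographs.

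Section 10.6 then makes four statements that bear on eye data:

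- General rule: "Continuous data items (e.g. HIT 6) will be analysed in the same way as the primary outcome".
- Two-eye rule: "For the visual function data which is collected in both eyes, it is expected that the participant's data will be correlated", so the primary analysis takes both eyes and "will be analysed using a linear mixed model, with participant included as a random effect".
- Single-eye analyses: "The visual function and papilloedema data for worst eye and best eye will also be analysed separately as per the primary outcome", and these are labelled secondary.
- Frisen grade: "A mean Frisen Grading will also be reported, and the data analysed as per the primary outcome".

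The model referred to is in section 10.5: "A linear regression model will be used to compare the ICP at 12 weeks between the two arms, adjusting for baseline ICP". It has no random effect, and needs none, because ICP gives one value per participant. OCT is not mentioned by name in section 10.6. The better/same/worse comparison with the baseline photograph goes to a chi-squared test, with no unit stated.

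**The concern.** The section recognises within-participant correlation and provides the remedy, but words it for only one of two outcomes measured on the same eyes. The single-eye sentence shows that papilloedema data are held for each eye and that one-eye analyses are not the main ones. The main papilloedema analysis therefore appears to use both eyes, while the only model named for Frisen grade has no term for the pairing.

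If an analyst put both eyes into that regression as separate rows, each participant would count twice. Confidence intervals for Frisen grade and OCT would be too narrow, and the two-sided 5% level promised in section 9.4 would not hold. If the analyst chose one eye, or the mean of both, the standard errors would be valid, but that choice would be made at analysis and not in the plan.

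**Working it through.** **1. Setting the text side by side**

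| Outcome (6.2) | Main model in 10.6 | How it gets there | Eye unit stated? |
|---|---|---|---|
| Acuity, perimetry, contrast sensitivity | Mixed model, participant random effect | Named directly | Yes, both eyes |
| Frisen grade | Plain regression of 10.5 | Named directly | No |
| OCT | Plain regression of 10.5 | General continuous-data rule only | No |
| Better/same/worse | Chi-squared test | Named directly | No |

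Other sections do not close the gap. Section 6.2 explains how several graders' readings become one grade per image, not how two eyes become one value per participant. Section 9.12 defines worst and best eye by baseline perimetry but does not choose either for the main papilloedema analysis.

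**2. Inputs for the size of the effect**

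The SAP gives no figure for the eye outcomes and no inter-eye correlation. From section 8 come 12 evaluable and 15 recruited participants per arm. Those reproduce: for a difference of 14 with SD 10, the two-sample t-test has power 0.877 at 11 per arm and 0.906 at 12, and 12/(1 − 0.20) = 15. They serve here only as numbers per arm. The inter-eye correlation after baseline adjustment, rho, is an assumption, taken from 0.3 to 0.9.

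**3. Formula, if both eyes are entered as separate rows**

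With n participants per arm, two eyes each and residual variance s²:

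- variance of the arm difference if eyes were independent: 2 × s²/(2n) = s²/n
- actual variance: 2 × s²(1 + rho)/(2n) = s²(1 + rho)/n
- true SE / naive SE = sqrt(1 + rho)
- large-sample type I error = 2 × [1 − Φ(1.96/sqrt(1 + rho))]

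For example, at rho = 0.5: sqrt(1.5) = 1.22, 1.96/1.22 ≈ 1.60, two-sided tail 11.0%.

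**4. Results**

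The simulated columns come from a baseline-adjusted ordinary regression on eye rows under no treatment effect, 8000 replicates per setting.

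| Assumed rho | True/naive SE | Naive/true SE | Type I, formula | Simulated, 12 per arm | Simulated, 15 per arm |
|---|---|---|---|---|---|
| 0.3 | 1.14 | 0.88 | 8.6% | 8.8% | 8.6% |
| 0.5 | 1.22 | 0.82 | 11.0% | 10.6% | 10.6% |
| 0.7 | 1.30 | 0.77 | 13.3% | 14.6% | 13.5% |
| 0.9 | 1.38 | 0.73 | 15.5% | 17.2% | 16.9% |

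**5. Same simulations, one value per participant**

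Regressing the mean of both eyes, or the worst eye alone, gave type I error between 4.6% and 5.3% across all settings. The inflation therefore depends entirely on which unit is used, and the SAP leaves that open.

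**The case against.** A reader might infer that the plan prescribes an invalid analysis and that the papilloedema standard errors will be too small. The documents do not support that. No sentence says that both eyes enter the regression as separate rows. The same cross-reference to the primary outcome describes the worst-eye and best-eye analyses, which have one value per participant and valid standard errors. The single-eye sentence covers visual function and papilloedema together and presents both as additional and secondary, so it reads naturally as a contrast with the mixed model just before it. The authors may well have meant papilloedema to share that model and used the term visual function loosely. A reader might also infer that OCT is expressly sent to the plain regression; it is not.

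Two further points are fair. Section 6.2 says both eyes explicitly only for visual function, so two-eye papilloedema data are an inference, though a sound one from the worst/best-eye sentence. And the SAP gives papilloedema no special rank among the secondary outcomes.

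All of this stands, and it makes the statistical harm conditional. It does not remove the defect. If the mixed model was intended, the Frisen sentence contradicts that intention. If it was not, the main analysis has no stated eye unit. Either way the text permits both a valid and an invalid analysis of the same data.

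**Conclusion.** The point holds as a defect of specification. Section 10.6 limits the both-eyes model to visual function, names for Frisen grade a regression that is unsuitable for paired-eye rows, leaves OCT to a general rule, and fixes no unit for any papilloedema analysis.

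The consequence is conditional. If both eyes are pooled as independent rows, reported standard errors are about 12% to 27% below the true ones, and the nominal 5% test rejects in about 9% to 17% of null trials. This rests on an assumed correlation of 0.3 to 0.9 after baseline adjustment. If one value per participant is analysed, type I error stays near 5%. No inflation was calculated for the chi-squared test, but it has the same unstated unit. Only secondary outcomes are touched; the primary ICP analysis is not.

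**What to change.** In section 10.6:

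1. Extend the mixed-model sentence to visual function and papilloedema data (OCT and Frisen grade), with the eye-level baseline value as covariate and participant as random effect.
2. Keep the worst-eye and best-eye regressions as secondary analyses for both outcomes.
3. Delete the cross-reference to the primary outcome from the Frisen sentence.
4. Apply the same rule to the better/same/worse comparison: either one value per participant, with its derivation stated, or a method that allows for two eyes per participant.

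An acceptable alternative to step 1 is to keep the plain regression and state the single value per participant that it uses, such as the mean of both eyes or the worst eye as defined in section 9.12. If the worst eye is chosen, the sentence calling that analysis secondary needs to change for papilloedema.

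The cost is a few lines of SAP wording. The mixed model is already planned for visual function and no further data are needed. Intervals will be wider than from pooled eyes, which is the correct result.

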## 8. Sample size

A total of 30 participants will be recruited, 15 participants in each group (AZD4017 vs. placebo).

To detect a difference between the groups of 14% in ICP (assuming a standard deviation of 10% for ICP) with 90% power and two-sided  $\alpha=0.05$ , requires 12 participants per group. Allowing for 20% drop out, 15 participants are required per group, so 30 participants in total.

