## 9.4. Levels of confidence and p-values

Unless otherwise specified, estimates of differences between groups will be presented with 95%, two-sided confidence intervals. P-values will be reported from two-sided tests at the 5% significance level.

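### The ordered worse/same/better photograph rating is tested with an unordered chi-squared test, and section 10.6 does not fix whether the unit is the eye or the participant

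*SAP*

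**What the plan says.** SAP section 6.2 lists fundus photographs as one of two measures of papilloedema. Masked neuro-ophthalmologists give each image a Frisen grade, and they are the readers "who also assess whether the image is better, worse or the same as the image taken at baseline".

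Section 10.6 then sets out the analysis:

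- For the Frisen grade and the comparison rating: "These data items will be presented as categorical data items at each time point". The mean Frisen grade is also analysed by the primary-outcome method, a linear regression adjusted for baseline.
- For the comparison rating: "The same, better or worse data will be analysed at 12 and 16 weeks using a chi-squared test". No ordinal or trend version, effect measure or unit of analysis is given.
- For visual function, where correlation between a participant's eyes is expected, data from both eyes "will be analysed using a linear mixed model, with participant included as a random effect". That sentence names visual function only.
- For the eyes singly: "The visual function and papilloedema data for worst eye and best eye will also be analysed separately as per the primary outcome". This is labelled a secondary analysis.

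Section 9.12 defines worst and best eye by baseline visual field mean deviation. On testing, section 9.4 says: "P-values will be reported from two-sided tests at the 5% significance level".

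**The concern.** There are two separate matters.

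**Ordering.** Worse, same and better form an ordered scale. Pearson's chi-squared statistic does not change when the columns are rearranged, so its two degrees of freedom are spread over all departures from equality, including patterns with no direction. The clinical question is directional: does papilloedema improve more on AZD4017? With about 12 evaluable participants per arm, the loss of power is worth avoiding.

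**Unit of analysis.** The rating is made per image, and the worst-eye and best-eye analyses imply images of both eyes. Section 10.6 provides for between-eye correlation in visual function but says nothing for this rating. The separate-eye papilloedema analyses follow the primary-outcome method, linear regression, which does not describe a chi-squared test on three categories. The analyst must therefore choose between one eye, each eye in turn, or all eyes together. One of these choices would not hold the 5% level.

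**Working it through.** **1. The plan's own figure.** Section 8 has a difference of 14%, SD 10%, 90% power and two-sided alpha 0.05: "To detect a difference between the groups of 14% in ICP". The normal formula gives n = 2 x (1.960 + 1.282)^2 x (10/14)^2 = 10.7, so 11 per arm. The t-test version gives 11.77, so 12. Then 12 / 0.8 = 15 per arm, 30 in total. The stated sample size reproduces, and 12 and 15 per arm are used below. It was set for ICP; the SAP gives no power figure for the photograph rating.

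**2. What ignoring order does.** Take invented counts at 15 per arm, better/same/worse: active 9/4/2, placebo 3/7/5.

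- Expected counts per arm are 6, 5.5 and 3.5. X^2 = 2 x (3^2/6 + 1.5^2/5.5 + 1.5^2/3.5) = 5.10 on 2 df, and p = exp(-5.10/2) = 0.078.
- Wilcoxon: active is better in 9 x 12 + 4 x 5 = 128 of 225 pairs, with 9 x 3 + 4 x 7 + 2 x 5 = 65 ties. U = 128 + 65/2 = 160.5, against 112.5 under the null. The tie-corrected variance is (225/12) x [31 - 3372/870] = 508.6, where 3372 is the sum of t^3 - t over column totals 12, 11 and 7. Then z = 48/22.55 = 2.13 and p = 0.033.
- Exchange the better and same columns. The Wilcoxon p becomes 0.89, but the chi-squared p stays at 0.078.

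**3. Power with one eye per participant.** The category splits are assumptions. Placebo better/same/worse is 25/50/25%. Active is 60/30/10% (A) or 65/30/5% (B). Power = sum over all pairs of arm outcomes of P(placebo outcome) x P(active outcome) x [p < 0.05], with multinomial probabilities. There are 91 x 91 tables at 12 per arm and 136 x 136 at 15, so no simulation error.

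| Per arm, split | Chi-squared | Wilcoxon, asymptotic | Gain | Wilcoxon, mid-p | Wilcoxon, exact |
|---|---|---|---|---|---|
| 12, A | 35.4% | 40.9% | 5.5 | 40.4% | 34.9% |
| 12, B | 46.6% | 56.8% | 10.2 | 55.7% | 48.9% |
| 15, A | 41.6% | 50.0% | 8.4 | 49.9% | 45.5% |
| 15, B | 56.2% | 67.6% | 11.4 | 67.1% | 62.3% |

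Under the null (25/50/25% in both arms), type I error is 5.4% for chi-squared, 4.7% to 4.9% for the asymptotic Wilcoxon, 4.5% to 4.7% for mid-p and 3.2% to 3.6% for the exact test.

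A second set of assumptions was simulated, 6,000 trials per setting. Control worse/same/better was 10/50/40, 20/50/30 or one third each, with a 1-SD latent shift. Chi-squared had 40% to 44% power against 50% to 53% for a linear trend test at 12 per arm, and 44% to 52% against 58% to 63% at 15. The gap is about 10 to 13 points.

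**4. If both eyes were pooled as independent rows.** With no treatment effect and an assumed latent between-eye correlation, simulated chi-squared type I error was:

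| Correlation | Type I error |
|---|---|
| 0.5 | 8% to 10% |
| 0.7 | 11% to 12% |
| 0.9 | 16% to 18% |

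As a check on scale, perfectly correlated eyes double the statistic, so the limit is P(2 x chi-squared on 2 df > 5.99) = exp(-5.99/4) = 22%. A trend test on pooled eyes is also inflated, about 9% to 16% over correlations of 0.5 to 0.9. Ordering and pairing therefore need separate remedies.

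**The case against.** The strongest case for leaving the plan alone is that the one-eye chi-squared test is valid and this rating is a supporting item. Type I error with one eye is close to 5%, even though nearly all such tables have an expected count below 5, so sparseness alone is not a fault. The Frisen grade from the same photographs is analysed by a regression that uses its ordering, and OCT also measures papilloedema. These points stand and limit the weight of the matter. They do not give a reason for discarding the order of this rating.

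The gain also depends on the replacement. An exact Wilcoxon test is conservative with this many ties: at 12 per arm under split A it has 34.9% power, no better than chi-squared at 35.4%. The gain belongs to the asymptotic or mid-p version, or to a trend test.

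Three stronger readings are tempting and not supported:

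- **That the plan pools eyes and so inflates false positives.** It nowhere says that both eyes enter the test. Labelling the separate-eye analyses secondary makes pooling a possible reading, but no more than that.
- **That section 9.4 is breached.** It allows for exceptions, concerns how estimates are presented and itself provides for p-values. Naming a test for one item does not clearly contradict it.
- **That the reader could not see the direction of effect.** The category counts planned in 10.6 show direction and rough size. Only a formal estimate with an interval is missing.

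**Conclusion.** The point holds as an inefficient test and an unfixed unit of analysis.

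The ordering criticism rests on the SAP's own text. Its size rests on assumed category splits: about 5 to 11 points of power at 12 to 15 per arm for splits A and B, and somewhat more for a 1-SD latent shift. The direction was the same in every setting examined.

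The pairing criticism is an omission. The figure of about 9% to 17% type I error applies only if eyes are pooled without adjustment, and it rests on assumed correlations of 0.5 to 0.9. It does not arise with one eye per participant or with each eye tested separately.

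The change is worth making because it is cheap and removes a choice that would otherwise be made with the data in hand. It has no bearing on the primary ICP analysis or the sample size.

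**What to change.** In section 10.6, replace the chi-squared sentence with text to this effect:

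*The worse/same/better rating will be compared between arms at 12 and 16 weeks, one eye per participant, with a two-sided tie-corrected Wilcoxon test (asymptotic or mid-p). The worst eye as defined in 9.12 is the leading analysis for this rating; the best eye will be analysed separately. The effect estimate is the probability that a participant on AZD4017 has a better rating than one on placebo, counting ties as one half, with its 95% confidence interval. If both eyes are combined, the method will account for clustering within participant.*

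A linear trend test would also serve. Name one version so that the choice is not left open. In the invented example above, the estimate would be 160.5/225 = 0.71.

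The text should say that the worst eye leads for this rating, because 10.6 otherwise treats separate-eye analyses as secondary. If a combined-eye analysis is wanted, its behaviour at 24 to 30 participants should be checked first. A proportional-odds model with a participant random effect has not been checked at that size.

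The cost is a short SAP amendment and minor reprogramming in the software already named in section 13. If the data have already been analysed, record the change under Appendix A.
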